### Statistical analysis

Statistical analyses of the clinical data will be performed by using SPSS statistics version 24 (IBM corp, Amonk, NY, USA). We will examine two different prediction models. In the prediction model for failure to become pregnant, the primary outcome will be defined as ‘not pregnant’ after the first fresh ET during IVF or IVF-ICSI treatment. In the prediction model for success to become pregnant, the primary outcome will be defined as ‘pregnant’. Normality of data will be determined by using the Shapiro-Wilks normality test. Continuous, normally distributed variables will be presented as mean with standard deviation, and variables with a skewed distribution as median with the range. Categorical variables will be presented as count and proportions.

Differences between the groups of women who will become pregnant and those who will not will be compared using Chi-square test or Fisher’s exact test for the categorical data, as appropriate. The Independent Samples t-test and Mann-Whitney U test will be used for continuous data. Two-sided *P* values less than 0.05 will be considered statistically significant. Applying the same method, differences between women with a favourable microbiome profile and those with an unfavourable profile will be compared.

Multivariate analysis will be performed using logistic regression with a selection of covariates that are known predictors for pregnancy outcome; age, duration of infertility and body mass index (BMI).

## Discussion

In the ReceptIVFity cohort study, the specificity and sensitivity of the urogenital microbiome composition for the prediction of IVF or IVF-ICSI outcome will be determined in a cohort of women of reproductive age who will be expected to undergo their first IVF or IVF-ICSI cycle on short term. ReceptIVFity will investigate the role of a broad range of bacterial species and the influence of other clinical parameters in the success rate of IVF or an IVF-ICSI treatment. Insights in the microbial profile and their impact on the success rate may allow for a new strategy to decide whether to continue with treatment or not. The ultimate goal will be to develop a predictive algorithm that enables identification of the group of women with a low chance to become pregnant prior to the start of the IVF or IVF-ICSI treatment. Women with a low a priori chance to become pregnant might prefer to avoid the unnecessary physical and emotional burden of a IVF or IVF-ICSI treatment with a high change of failure.

### Strengths

The ReceptIVFity study will be the first cohort study in which the microbial composition will be used as predictor for IVF or IVF-ICSI outcome prior to the start of the treatment. As mentioned in the background section, several studies have found associations between the presence of microorganisms and reproductive outcomes, such as decreased implantation, pregnancy, ongoing pregnancy, and live birth rates. However, the clinical applicability of these findings has not yet been integrated into daily practice.

The ReceptIVFity cohort study consists of a large patient group/sample size and well-defined patients. A large sample is indicated, anticipating the fact patients can drop out for further treatment/follow up due to several reasons, such as poor response or total fertilisation failure. The included patients with embryo transfers will be used to investigate an association between microbial composition and IVF or IVF-ICSI outcome.

A prospective study design blinded for the test result, avoids bias to continue or not continue the treatment and allows for unbiased follow-up of the treatment outcomes.The 1 year follow-up is needed to examine the sustainability of the predicted outcome and will provide insight into the possibilities of becoming pregnant with subsequently performed IVF or IVF-ICSI procedures. Different techniques can be used to assess the microbiome and a high throughput technique is desirable for future application in daily practice. The prospective study validates the findings from the pilot study by the use of two different techniques. NGS that has become a gold standard for categorising bacteria or characterising microbial communities and the IS-pro technique which has the benefit of presenting results within 5 hours will be compared in this study. In addition, two sample sites (urine samples and vaginal swabs) will be compared with each other, both sites are easy to obtain by patients themselves. Developing a predictive test based on the urogenital microbiome composition will contribute to a personalised medicine approach in the future.

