### Study population

Women who will visit the infertility outpatient clinics of participating hospitals and who are expected to undergo their first IVF or IVF-ICSI cycle within the next 2 months will be approached to participate in this study. Inclusion criteria to be fulfilled are: women aged between 20 and 44 years and a male partner. Those excluded from the study will be: women with an indication for emergency IVF because of cancer or other reasons, endometriosis American Fertility Score (AFS) III/IV and pre-treatment with a Gonadotrophin-releasing hormone (GnRH) analogue or those who use hormonal contraceptives within 3 months prior to the start of their IVF or IVF-ICSI intake. Those women who are using the oral contraceptive pill for the purpose of cycle timing prior to their treatment cycle will be eligible for this study. Women who have had a previous pregnancy or miscarriage in their medical history will also be excluded from participation. Pregnancy outcomes after the first fresh ET will be used as endpoint for this study. Ongoing pregnancy is defined as an intrauterine embryo/foetus with detection of cardiac activity on transvaginal ultrasound between 7 and 9 weeks of gestation.

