### Study materials

A vaginal swab and a midstream urine sample before the start of the IVF or IVF-ICSI procedure will be self-collected. The swab and the urine sample have to be taken within the 2 months prior to the ET. A self-collecting method was chosen, because it is minimally invasive and therefore suitable for use in daily practice. Vaginal samples will be taken with FLOQSwabs™ (Copan Italia SpA, Brescia, Italy). The participants will be instructed to insert the swab 3–5 cm beyond the vaginal orifice, and move the swab around along the vaginal wall for 10–15 s. After this procedure the swabs will be immediately placed in Eppendorf tubes filled with reduced transport fluid (RTF) buffer (Microbiome Ltd., Amsterdam, the Netherlands). Until further processing, samples will be stored in a freezer at − 20 °C degrees.The urine sample collection will be obtained according to a standard ‘clean catch’ protocol, including washing hands thoroughly, cleaning the urinary opening with towelettes and collecting a midstream specimen in a sterile container. The urine sample will be stored at room temperature or in the refrigerator at 2–8 °C for a maximum of 2 hours until further processing. Further processing will consist of vortexing the urine sample and centrifuging 10 ml of the urine at 1500 relative centrifugal force (RCF) followed by resuspension in 1 ml of urine, which will be stored at -20 °C degrees until transport.Next, vaginal swabs and urine samples will be transported on dry ice by courier from the eight clinics to the microbiological laboratory.

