### Microbiome analysis and algorithm building

The vaginal microbiome profile of each participant will be assigned to one of five community state types (CST) based on the dominant microbial species, as described by Ravel et al.^10^ Microbial communities in group I are dominated by *L. crispatus,* whereas group II, III, and V are dominated by respectively *L. gasseri, L. iners,* and *L. jensenii.* Group IV contains a heterogeneous group including species such as *Prevotella*, *Dialister*, *Atopobium*, *Gardnerella*, *Megasphaera*, *Peptoniphilus*, *Sneathia*, *Eggerthella*, *Aerococcus*, *Finegoldia*, and *Mobiluncus.*

The prediction model will be composed by analysis of the microbiological data will be performed in Spotfire 7.6 (TIBCO Spotfire Inc., Somerville, MA, USA). First, a distance matrix will be created on cosine distances of all possible sample pairs. Cosine distances are calculated with the following formula:

$$ \mathrm{dissimilarity}=1-\mathit{\cos}\left(\theta \right)=1-\frac{\sum_{i=1}^n{A}_i\times {B}_i}{\sqrt{\sum_{i=1}^n{\left({A}_i\right)}^2\times}\sqrt{\sum_{i=1}^n{\left({B}_i\right)}^2}} $$

The resulting data will be clustered with the unweighted pair-group method with arithmetic mean (UPGMA)4 and plotted as a heatmap.

To answer the questions of this study, an algorithm will be built based on the composition of the vaginal microbiome profile. First, the algorithm will be built by exploration of the pregnancy outcomes per CST. In a subsequent step, the data will be analysed for species content and microbial diversity per phylum. The formula will be validated for prediction of failure to become pregnant after (the first) fresh embryo transfer during the IVF or an IVF-ICSI treatment. Sensitivity will be calculated as true positive (TP) / (TP + false negative (FN)) and specificity as true negative (TN) / (TN + false positive (FP)). Predictive accuracy will be determined as the correlation between the predicted outcome and the actual outcome.

The vaginal samples that meet the prediction model for failure to become pregnant will be defined as ‘unfavourable microbiome profiles’. The vaginal samples that will not comply with the prediction model for failure to become pregnant will be defined as a ‘favourable microbiome profile’. Additionally, we will explore whether we can stratify these samples with a favourable microbiome profile into an average and a high chance to become pregnant based on additional bacterial species.

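### Accuracy for the primary fresh-transfer endpoint is estimated in women who reach embryo transfer, but the test is meant for women deciding before treatment, so the pregnancy chance per profile will generally be overstated for them

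*Protocol article*

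**What the plan says.** The primary endpoint is tied to the first fresh transfer throughout the Methods. Study population: "Pregnancy outcomes after the first fresh ET will be used as endpoint for this study". Microbiome analysis and algorithm building: "The formula will be validated for prediction of failure to become pregnant after (the first) fresh embryo transfer". Statistical analysis defines the failure outcome as not being pregnant "after the first fresh ET during IVF or IVF-ICSI treatment".

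Strengths justifies the sample size by "anticipating the fact patients can drop out for further treatment/follow up due to several reasons, such as poor response or total fertilisation failure", and the next sentence names the analysis set: "The included patients with embryo transfers will be used to investigate an association between microbial composition and IVF or IVF-ICSI outcome".

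The intended use comes earlier in the patient's course. The Discussion gives the ultimate goal as "identification of the group of women with a low chance to become pregnant prior to the start of the IVF or IVF-ICSI treatment". Background speaks of selecting women who should not undergo treatment, and In summary foresees a routine test before treatment. The first paragraph of the Discussion also describes the cohort as women expected to undergo a first cycle, not as women who had a transfer.

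Study aim gives embryo implantation failure as the primary objective. Limitations does not mention women who start a cycle and never reach transfer.

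**The concern.** Whether a woman enters the primary analysis depends on an event after the test sample: she must respond to stimulation, have fertilised oocytes and receive an embryo. A couple using the test beforehand cannot know whether that will happen. Poor response and fertilisation failure are part of the risk they are weighing, yet the plan handles them as drop-out.

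Two things are at stake. First, the pregnancy chance quoted for a profile is calculated without a group of treatment failures. The plan also intends to divide favourable profiles into an average and a high chance of pregnancy, and these are the figures most exposed. Second, if the profile is related to reaching transfer, an analysis confined to women with a transfer cannot show it, and the sensitivity it reports may be too high or too low for the population tested.

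**Working it through.** The protocol gives no transfer rate and no accuracy figure for all starters, so there is no planned figure to reproduce. The check compares two denominators.

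**Inputs from the protocol.** 300 women (Abstract, Methods); about 25% pregnant at the first attempt (Background); pilot sensitivity 81% and specificity 96% (Background).

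**Assumptions.** The share reaching fresh transfer, T, is varied. A positive test means predicted failure. Women without a fresh transfer count as not pregnant from that cycle.

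**1. Overall pregnancy rate, reading 25% as per started cycle.** Pregnant: 300 × 0.25 = 75; not pregnant: 225. Per-transfer rate = 75 / (300 × T).

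| No fresh transfer | Analysed | Per-transfer rate | Share of failures left out |
|---|---|---|---|
| 10% (30) | 270 | 75/270 = 27.8% | 30/225 = 13% |
| 20% (60) | 240 | 75/240 = 31.3% | 60/225 = 27% |
| 25% (75) | 225 | 75/225 = 33.3% | 75/225 = 33% |

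If 25% is instead per transfer, the chance per woman sampled is 0.25 × T: 22.5%, 20.0% and 17.5% at T = 90%, 80% and 70%.

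**2. By profile, with pilot accuracy, 25% per transfer and T = 80%.** 240 women have a transfer: 60 pregnant, 180 not.

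- Failures with an unfavourable profile: 0.81 × 180 = 145.8; with a favourable profile: 34.2.
- Pregnant with a favourable profile: 0.96 × 60 = 57.6; with an unfavourable profile: 2.4.
- Favourable-profile pregnancy chance per transfer: 57.6 / (57.6 + 34.2) = 62.7%.
- Unfavourable-profile failure probability per transfer: 145.8 / 148.2 = 98.4%.

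Now add the 60 women without transfer. If profile is unrelated to reaching transfer, a share 148.2/240 = 0.6175 of them is unfavourable, so 37.05 unfavourable and 22.95 favourable.

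- Favourable-profile pregnancy chance per woman sampled: 57.6 / (57.6 + 34.2 + 22.95) = 50.2%.
- Sensitivity: (145.8 + 37.05) / 240 = 76.2%, against 81%.
- Unfavourable-profile failure probability: 182.85 / 185.25 = 98.7%.
- Specificity: 57.6 / 60 = 96%, unchanged, because every woman pregnant after a fresh transfer had one.

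**3. If profile is related to transfer (T = 80%).**

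- All 60 favourable: sensitivity 145.8/240 = 60.8%; favourable-profile chance 57.6/151.8 = 37.9%.
- All 60 unfavourable: sensitivity 205.8/240 = 85.8%; favourable-profile chance unchanged at 62.7%.

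**4. Other transfer rates.** With profile unrelated to transfer, the favourable-profile chance is 62.7% × T: 56.5%, 50.2% and 43.9% at T = 90%, 80% and 70%. Across T = 70% to 95% and every split of the non-transferred women, the unfavourable-profile failure probability stays between 98.4% and 99.0%.

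**The case against.** The strongest defence is that the primary objective is implantation failure, which requires a transfer, and that the Methods use the first fresh transfer consistently. That stands: the per-transfer analysis is right for that objective. It does not support the claims about use before treatment. The restriction is written into the article, so it is not a detail left to an unseen plan. The Abstract does say that accuracy will be validated only for fresh transfer, but it contrasts this with frozen transfers and later cycles, not with women who start and have no transfer.

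A reader might infer more than the protocol supports:

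- **That the measure the plan calls crucial is biased.** It is not. Background names specificity, which is unchanged. Adding failures can only hold or raise the failure probability for an unfavourable profile, so on that side the per-transfer figure is conservative.
- **That the whole study is confined to transfers.** The one-year endpoint runs from inclusion, and no transfer restriction is stated for it.
- **That every woman without a fresh transfer is a non-pregnancy.** This holds for poor response and fertilisation failure leading to no transfer. A freeze-all cycle can still lead to pregnancy from a later transfer.
- **That the sampling window is a second filter.** Study population approaches women "expected to undergo their first IVF or IVF-ICSI cycle within the next 2 months", while Study materials says: "The swab and the urine sample have to be taken within the 2 months prior to the ET". The first governs when women are approached and the second when samples are taken. A woman approached early can be sampled later and satisfy both. Nothing says that samples outside the window are removed from the analysis.

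**Conclusion.** The point holds for the primary fresh-transfer endpoint, as a mismatch between analysis set and intended use. It is not a fault in the per-transfer analysis itself.

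The direction for the overall pregnancy chance is certain once some women have no transfer because of poor response or fertilisation failure: the per-transfer figure is too high for a woman deciding beforehand. The favourable-profile chance is too high unless none of those women has a favourable profile. Sensitivity can move either way.

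The size rests on transfer rates that the protocol does not give. A true 25% per started cycle would read as 28-33% per transfer if 10-25% have no fresh transfer; these are upper-end figures if some of those cycles are freeze-all. The fall from 62.7% to 50.2% for a favourable profile also depends on accuracy figures from a pilot of 42 women and on profile being unrelated to transfer. So does the finding that the unfavourable-profile failure probability hardly moves: it depends on the pilot's accuracy being confirmed. No figure in the protocol is contradicted. The change should be made, because the quoted chances are what couples would act on.

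**What to change.** Keep the per-transfer analysis for the implantation objective. Add, as the analysis that supports the pre-treatment claim, sensitivity, specificity, predictive values and pregnancy chance per profile in all sampled women who start their first cycle. Count absence of a transfer due to poor response or fertilisation failure as not pregnant from that cycle. Report freeze-all cycles separately, by the outcome of their first transfer. Report how many sampled women reached fresh transfer, by profile, so that any link between profile and transfer is visible.

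If this analysis is not added, restrict the claims in the Discussion and In summary to women who reach a fresh transfer, and list the selection under Limitations.

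The cost is one further analysis, with no new women or samples; it needs the first-cycle outcome of every sampled woman who starts. The downside is two sets of figures to explain and a freeze-all rule that must be written down.

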### Limitations

Because our study uses a well-defined study population, the results will be limited to the IVF or IVF-ICSI population. Whether these results also apply to a general population trying to establish a pregnancy and without ART cannot be extrapolated from these data.

In our study, we collect the samples only once and prior to the start of the first treatment cycle.

The success rate of IVF or IVF-ICSI treatment depends on multiple clinical parameters. Account must be taken for possible confounders in order to develop an independent test for prediction of IVF or IVF-ICSI outcome. Nevertheless, we will collect these clinical data (e.g. age, BMI, duration of infertility) and will correct for these possible confounders.

### In summary

In the future, microbiome profiling can be a routine diagnostic test prior to IVF or IVF-ICSI treatment if the negative predictive value is high enough to prevent patients a treatment with emotional and physical burden, that has low chance of success. With this cohort, we aim to contribute to better insight and validation of the urogenital microbiome as predictor for IVF or IVF-ICSI outcome. Finally, our ultimate goal is development of a diagnostic test that enables couples to make a more substantiated decision on whether to continue with treatment or not, based on their personal and individual microbiome profile.

## Abbreviations

AFS: American Fertility Score
ART: Assisted Reproductive Technologies
BMI: Body mass index
CST: Community state type
DNA: Deoxyribonucleic acid
ET: Embryo transfer
FAFV: *Fusobacteria* and *Verrucomicrobia*
FN: False negative
FP: False positive
GnRH: Gonadotrophin-releasing hormone
ICSI: Intra Cytoplasmic Sperm Injection
IS: Intergenic spaces
IVF: In-vitro Fertilization
NGS: Next generation sequencing
OTU: Operational Taxonomic Units
PCR: Polymerase chain reaction
RCF: Relative centrifugal force
RFU: Relative fluorescence units.
RTF: Reduced transport fluid.
TN: True negative
TP: True positive
UMC: University Medical Centre
UPGMA: Unweighted pair-group method with arithmetic mean
